### Ethical considerations

A facility staff member will identify potential residents and their carers and seek agreement from the carer to be contacted by the research team. Since the residents concerned will have dementia, often to a moderate or severe degree, the family carer (or significant other person) who visits most frequently will be asked for written informed *consent*, on his/her own behalf and on behalf of the person with dementia, in accordance with both the Monash University HREC and the Victorian Civil and Administrative Tribunal. Persons with dementia must also *assent *to participate in the study. If it is clear from their demeanour or behaviour that they do not wish to participate, their participation in the study will be discontinued.

Carers will either directly commence with the Montessori training and implementation or will be told that due to limited resources they will be put on a waiting list for four weeks (the control condition). We will ask them to complete the baseline and all follow-up measures and to attend a dementia education session. Carers will be blinded to the hypotheses of the study and the purpose of the waiting list option. After the carers in this condition complete the measurements associated with the control period, they will be debriefed regarding the purpose of the waiting list option and are invited to participate in a Montessori workshop.

### Setting

The study will be conducted in mainstream and psychogeriatric aged care facilities in the state of Victoria, Australia. Preference will be given to larger facilities (≥ 60 beds).

### Recruitment

Aged care facilities will be contacted by telephone to explain the studies. If facilities show interest in the study, researchers will visit the facility to provide all relevant parties (director of nursing, nursing staff and diversional therapists) with more detailed information. If facilities consent to participate in the study, a pre-selection screening will be conducted to identify eligible participants. An appointed delegate of the facility will then contact the identified family carers to ask if they consent with forwarding their contact details to a Monash University researcher. When verbal consent is given a senior researcher will contact the carer to explain the study and answer queries. If carers express interest in the studies they will be sent a Participant Information and Consent Form package. Once written consent is received, researchers will gather baseline information and plan the training session with groups of up to six participants. If more than six family carers are eligible and interested in the study in a particular facility, more training sessions will be organised.

### Participants

#### Inclusion criteria for residents

(i) A chart diagnosis of dementia or probable dementia; and (ii) residency in the facility for ≥ 3 months to allow for adjustment to the new setting.

#### Exclusion criterion for residents

Acute life-threatening illness as reported by nursing staff.

#### Inclusion criteria for family carers

(i) Visit regularly ≥ 2 times per week for 30 minutes or more to match study requirements, (ii) willing to follow study protocol, and (iii) sufficient fluency in English to understand the workshop and fill out questionnaires.

### Experimental conditions

#### Montessori-based activities

Family carers will be trained in the principles underpinning Montessori activities in three-hour group sessions in their relative's facility. A pair of researchers will conduct these workshops. They will spend half an hour helping carers to fill out the baseline questionnaires; an hour explaining the theoretical basis of Montessori activities in dementia, and an hour and a half in smaller groups brainstorming and practising possible activities.

Carers will choose up to 10 activities based on their relative's former interests and current motor and language skills. For the purpose of continuity of the intervention after the study finishes, carers will be asked to prepare materials using their own and the facilities materials. The mode of delivering activities can be easily adapted to residents' cognitive status, making it possible to include people with mild through to very severe dementia. For example, a suitable activity for a former mechanic with moderate dementia might include discussing the characteristics and qualities of period cars shown in laminated photographs. If dementia is severe, the activity can be simplified to sorting the photographs into categories based on colour, or preference.

#### Control condition

The control condition should match the level of contact with the researchers and additionally control for the effects of the carers meeting each other as part of the group training. To ensure comparability with the experimental condition, the family carers will receive a dementia education session lasting three hours. Again, the first half hour will be spent filling out the baseline questionnaires; an hour and a half will be used for dementia education after which the groups will split into smaller groups to discuss the material just presented. To match the involvement of the relatives with dementia, we will ask carers towards the end of the training session to spend some time with their relative. During this time, the researchers will spend time with every couple, introducing themselves to the residents and engaging in general conversation with them.

### Outcomes measures

#### Primary measure

##### Quality of visits

We will ask carers to rate their overall satisfaction with each study visit on a 5-point Likert scale. In addition, they will complete a truncated version of the Pearlin Mastery Scale [26] adapted to care-related situations [27], focussing on their sense of personal mastery during each visit. Pioli (2010) [27] deleted two items of the original scale, because they were not specifically related to carer interactions: 'Sometimes I feel that I'm being pushed around in life' and 'What happens to me in the future mostly depends on me'. The remaining items will be reworded to make them relevant to visits, for example 'I had little control over the things that happened today when I spent time with my family member' and 'I felt helpless in dealing with the problems I experienced during my visit today'.

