**Methods/Design:**

We will conduct a cluster-randomised trial to train family carers in conducting personalised one-to-one activities based on the Montessori methodology with their relatives. Montessori activities derive from the principles espoused by Maria Montessori and subsequent educational theorists to promote engagement in learning, namely task breakdown, guided repetition, progression in difficulty from simple to complex, and the careful matching of demands to levels of competence. Persons with dementia living in aged care facilities and frequently visiting family carers will be included in the study. Consented, willing participants will be randomly assigned by facility to a treatment condition using the Montessori approach or a control waiting list condition. We hypothesise that family carers conducting Montessori-based activities will experience improvements in quality of visits and overall relationship with the resident as well as higher self-rated mastery, fewer depressive symptoms, and a better quality of life than carers in the waiting list condition.

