### Study protocol

The study period will be brief to reduce the likelihood that changes in outcomes are due to dementia progression, inter-current illness or other incidental events. Activity sessions must be long enough to detect changes in selected outcomes during the carer's visit, but not so long that sessions are likely to be interrupted by meals or nursing interventions. In our recently completed Montessori study [25], the choice of 30-minute sessions has worked well. A study period of up to four weeks has also proved feasible. We will therefore employ an exposure of six sessions spread over a three week period for both conditions. The choice of condition (treatment or control) will be randomly determined using Excel. The program from week 1 (W1) to week 5 (W5) is shown in Table 1. Baseline measures will be conducted at the start of the Montessori workshop or dementia education session (W1). All participants will receive a follow-up phone call half way through W2-W4 to ascertain they have filled out questionnaires after each visit. A face-to-face appointment will be made to complete the final measurements at the end of W4.

**Table 1 T1:** Program for treatment and control condition groups

	Treatment group	Control group
W1	Group Montessori workshop	Dementia education session

	↓	↓

W2 W3 W4	6 Montessori sessions	Waiting list period

		↓

W5		Group Montessori workshop

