#### Secondary measures

All of the following secondary measures will be completed at baseline and at the end of the three-week study period.

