##### Carer's mastery

Carers will complete five items of the Pearlin Mastery Scale matching the items administered at the end of every study visit but using the scale's original wording describing global mastery [26]. These items include, "I have little control over the things that happen to me" and "There is really no way I can solve some of the problems I have". This shortened scale has a high internal consistency with an *alpha *of 0.72 [27].

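### Quality of visits, the primary outcome, is the only outcome without a pre-intervention rating, so it cannot be adjusted for its own baseline

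*Protocol article*

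**What the plan says.** Under Primary measure (Quality of visits), the article states: "We will ask carers to rate their overall satisfaction with each study visit on a 5-point Likert scale". The second component is a shortened Pearlin Mastery Scale, "focussing on their sense of personal mastery during each visit", with items worded for the visit made that day.

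The timing is given under Study protocol and in Table 1. W1 holds the Montessori workshop or the dementia education session, and baseline measures are taken at its start. The visits follow in W2 to W4. All participants get a "follow-up phone call half way through W2-W4 to ascertain they have filled out questionnaires after each visit".

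Under Secondary measures: "All of the following secondary measures will be completed at baseline and at the end of the three-week study period". Other measures adds further baseline items: socio-demographic details, type of relationship, duration of caring, visit frequency and length, pre-morbid relationship, dementia severity (CDR) and agitation. None of these rates a visit.

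The nearest baseline item to the primary outcome is global mastery: "Carers will complete five items of the Pearlin Mastery Scale matching the items administered at the end of every study visit", but in the original general wording.

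Statistical analysis plans t-tests on arm means, then ANOVAs, then ANCOVAs that control for other measures to explore mediation, and finally multilevel versions that include the facility.

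**The concern.** The schedule gives a starting value to every outcome except the primary one. Whole facilities are allocated and about 50 carers are recruited, so the arms may differ by chance in how satisfying visits already were. A pre-intervention rating of the same outcome is usually the strongest covariate available for removing such a difference and for reducing residual variance. It is also the only way to describe how much an individual carer's visits improved. This gap cannot be closed later: an analysis plan can choose among collected data, but it cannot supply a rating that had to be made before W1.

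**Working it through.** **1. Is there a pre-W1 rating anywhere?**

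| Outcome | Before W1 session | W2-W4 | End |
|---|---|---|---|
| Visit satisfaction (primary) | none stated | after each study visit | - |
| Visit mastery (primary) | none stated | after each study visit | - |
| Relationship rating, Mutuality, global mastery, CES-D, Carer-QoL | yes | - | yes |

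Two possible sources of a hidden baseline fail. The half hour of questionnaires that opens the W1 session does not suit items about a visit just made. The time control carers spend with their relative at W1 comes towards the end of the session, with researchers present, and is described for that arm only.

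**2. What the planned comparison estimates.** Under randomisation the expected baseline difference between arms is zero, so the post-intervention difference in means estimates the treatment effect without bias. The loss is therefore in precision and in protection against the imbalance of the one realised allocation. Within-carer change is also unavailable.

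**3. The plan's own sample size, as reference.** From Sample size calculation: d = (3.48 - 2.89)/0.74 = 0.797, taken as 0.80, with alpha 0.05 and power 0.80. An exact two-sample t calculation gives 20.03, rounded up to 21 per arm, if alpha is one-sided; this reproduces the stated 21. Two-sided it gives 25.52, rounded up to 26. The article does not state the sidedness. At 21 per arm, two-sided power is 0.716. The effect size comes from Mutuality, so it serves here only as a yardstick.

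**4. What an own baseline would buy.** Let r be the correlation between the usual-visit rating and the primary outcome (assumed). Adjustment leaves a fraction 1 - r² of the variance. The equivalent gain in sample is 1/(1 - r²). Power is for d/sqrt(1 - r²), 21 per arm, two-sided 0.05, ignoring clustering.

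| r | Variance left | Variance removed | Equivalent sample | Power |
|---|---|---|---|---|
| 0 | 1.00 | 0% | 1.00 | 0.716 |
| 0.3 | 0.91 | 9% | 1.10 | 0.755 |
| 0.5 | 0.75 | 25% | 1.33 | 0.832 |
| 0.7 | 0.51 | 49% | 1.96 | 0.943 |

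These gains are measured against no covariate at all. Against a model that already holds global mastery, Mutuality and CDR they would be smaller. How much smaller cannot be worked out from the article.

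**5. Chance imbalance.** The SD of the arm difference at baseline, in outcome SDs, is sqrt((2/n)(1 + (m - 1)ICC)), where m is carers per facility. With n = 21 and no clustering it is sqrt(2/21) = 0.31. With m = 6 (assumed) it is 0.35, 0.38 and 0.44 at ICC 0.05, 0.10 and 0.20 (assumed). An imbalance of 0.31 moves the unadjusted estimate by r × 0.31: 0.09 at r = 0.3, 0.16 at r = 0.5 and 0.22 at r = 0.7, against a planning effect of 0.80.

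**The case against.** The strongest reply is that a post-only randomised comparison is an accepted design, and that the instrument is tied to individual visits by intention. That stands, and it rules out several stronger readings.

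- A reader might infer that the hypothesised improvement cannot be measured. The abstract does say carers "will experience improvements in quality of visits and overall relationship with the resident", but the sentence goes on to compare them with waiting-list carers, and the Background repeats the comparison. The hypothesis is between arms and remains testable.
- A reader might infer that chance differences cannot be adjusted for at all. Matching-item global mastery, relationship quality, Mutuality, CDR, agitation and relationship type are all collected at baseline and permit partial adjustment. Their limits are that global mastery mirrors only one of the two primary components and asks about life in general, that visit satisfaction has no matching baseline item, and that the ANCOVAs are presented as exploring mediation.
- A reader might see a contradiction in the Study protocol section: "Activity sessions must be long enough to detect changes in selected outcomes during the carer's visit". That sentence explains the length of a session and promises no pre-post measurement.
- The imbalance in step 5 is ordinary sampling error, which a correct test already allows for. It is not bias. The multilevel model can carry facility variation into the standard error, though it does not remove the realised imbalance.
- The number of facilities is not stated. Fifty carers in groups of up to six means at least 9 training groups (50/6 = 8.3), but one facility may host several, so nothing can rest on there being few.

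It may also be said that the article is condensed and does not itemise every baseline questionnaire. But it does fix the timing: the visit form belongs to study visits, and the baseline-and-end schedule is attached to the secondary measures.

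**Conclusion.** The point holds in a limited form. Quality of visits is the only outcome with no pre-intervention rating in either arm. The randomised post-intervention comparison is valid. Within-carer improvement in visit quality cannot be measured, and adjustment of the primary outcome for its own baseline is not possible. The cost is in precision and in protection against chance imbalance: 9% to 49% of residual variance for an assumed r of 0.3 to 0.7, and less than that once the proxies are used. At r = 0.3 the gain is modest; at 0.5 or above it matters in a trial of about 50 carers. The values of r, the ICC and the six carers per facility are assumptions, and the power figures ignore clustering. That the baseline is absent rests on the printed schedule alone. This is an inexpensive improvement worth making, and the absence does not invalidate the trial.

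**What to change.** After written consent and before the W1 session, with allocation not yet disclosed, have every carer in both arms complete the existing visit form (the satisfaction item and the five visit-mastery items) after two usual visits. Add this to the schedule in Table 1. Use the mean of the two ratings of each component as the baseline covariate for that component in the primary-outcome model, alongside the planned facility-level (multilevel) term.

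Cost: two copies of a six-item form per carer. Eligible carers already visit at least twice a week, so no visit is added. The Recruitment section already has researchers gathering baseline information once consent is received, so the forms can go out at that step; sending them with the consent package would put them ahead of consent. The downsides are about a week between consent and W1, a slight form burden, and a small chance of cueing carers to the outcome, equal in both arms. Invitations to the W1 session must not reveal which session it is until the forms are returned.

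If the forms cannot be added, state that the primary analysis is a post-intervention comparison adjusted for baseline global mastery and relationship quality, with facility as a random effect.

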### Statistical analysis

We will use independent t-tests to compare the means of outcome measures for the Montessori and control conditions. Next, each outcome measure will be subjected to a 2-way ANOVA with condition (Montessori *vs*. control) as fixed factor. We will then undertake ANCOVAs to investigate whether the intervention enhances certain outcomes (e.g. quality of relationships) after controlling for others (e.g. quality of pre-morbid relationships) to explore the possibility of mediation. Secondly, we will extend these models to examine whether other factors, such as resident-carer relationship (e.g. spouse *vs*. child) and dementia severity (moderate *vs*. severe) serve to moderate treatment benefits. Finally, we will conduct a multilevel variant of these ANOVAs to include higher level factors such as the aged care facility.

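### The primary measure is rated after each of about six visits per carer, but no analysis as specified fits ratings nested in carers nested in randomised facilities

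*Protocol article*

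**What the plan says.** All places are in the Methods/Design part of the Protocol article.

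- **Quality of visits (primary measure).** There are two instruments, both tied to the visit. For satisfaction: "We will ask carers to rate their overall satisfaction with each study visit on a 5-point Likert scale". For the shortened mastery scale: "focussing on their sense of personal mastery during each visit".
- **Study protocol.** "We will therefore employ an exposure of six sessions spread over a three week period for both conditions". A phone call part-way through W2-W4 checks with all participants "to ascertain they have filled out questionnaires after each visit". Each carer in either arm should therefore supply about six ratings on each instrument.
- **Secondary measures.** These have two fixed time points, baseline and the end of the three weeks. The primary measure has no corresponding single time point.
- **Statistical analysis.** The first step is: "We will use independent t-tests to compare the means of outcome measures for the Montessori and control conditions". Then "each outcome measure will be subjected to a 2-way ANOVA with condition" as the only factor named. ANCOVAs and moderator models follow. The last step is: "Finally, we will conduct a multilevel variant of these ANOVAs to include higher level factors such as the aged care facility".
- **Study design.** Condition is allocated by facility.

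**The concern.** An independent-samples t-test needs one independent value per carer. The primary measure gives about six correlated values per carer, and the analysis section does not say which value, or which summary, enters the test. The multilevel step does not settle this. It comes last, and it looks upward to the facility rather than downward to visits within a carer.

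The data have three levels: rating, carer and facility. The lead test respects neither of the two groupings. The closing model is described only for the upper one. Different analyses compatible with the text can give different answers from the same 50 carers, with different error rates and different power, and this affects the outcome on which the trial will be judged.

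**Working it through.** **The plan's own figures.** The documents state no error rate or power for the primary measure. The sample size is 21 per condition, from a two-group t-test on the Mutuality Scale, a secondary measure: (3.48 - 2.89)/0.74 = 0.797, rounded to 0.80. With alpha 0.05 and power 0.80, 21 is reproduced by a one-sided test (20.03, rounded up); a two-sided test needs 26. That is a separate point. What matters here is that the calculation counts carers, one value each.

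**Inputs.**
- From the documents: six visits, alpha 0.05, and 50 carers less 20% = 40, so 20 per arm.
- Assumed: two-sided testing, equal correlation rho between any two visits of the same carer (range 0.2 to 0.8) and, at first, no facility effect.

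**False-positive rate if all ratings are pooled as independent.** There are 40 x 6 = 240 ratings. The true variance of the arm difference exceeds the assumed one by a factor 1 + (6 - 1) x rho, so the rate is about 2 x [1 - Phi(1.96 / sqrt(1 + 5 rho))]. At rho = 0.5 the factor is 3.5, 1.96/sqrt(3.5) = 1.048, and the rate is 29.5%.

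**False-positive rate if any one of six visit-by-visit tests may count.** With independent visits it would be 1 - 0.95^6 = 26.5%. Correlation lowers it, as simulation shows.

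Simulation: 20,000 null trials per row, 20 carers per arm, six visits.

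| rho | Pooled, formula | Pooled, simulated | Any of six visits | Carer mean |
|---|---|---|---|---|
| 0.2 | 16.6% | 16.4% | 25.2% | 4.9% |
| 0.3 | 21.5% | 21.4% | 23.8% | 5.2% |
| 0.5 | 29.5% | 30.0% | 21.1% | 5.1% |
| 0.7 | 35.6% | 36.7% | 16.8% | 4.9% |
| 0.8 | 38.1% | 39.0% | 13.9% | 5.0% |

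A simulation at rho = 0.5 with 21 per arm and ratings cut to a 5-point scale gave 28.9% for pooling, so the coarse scale hardly matters.

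**Power if one visit is used instead of the mean.** The variance of a carer mean relative to one visit is (1 + 5 rho)/6, that is 0.42, 0.58 and 0.75 for rho 0.3, 0.5 and 0.7. For an assumed true effect of 0.5 single-visit SD, the standardised effect on the mean is 0.5/sqrt of these: 0.77, 0.65 and 0.58. With 20 per arm, power is 34% for one visit and 67%, 52% and 43% for the mean.

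**Facility effect on the carer-mean t-test.** Assume 6 carers per facility and an intraclass correlation of carer means of 0.01, 0.05 or 0.10. The variance factor is 1 + 5 x ICC = 1.05, 1.25 or 1.50, and the false-positive rate of an unadjusted t-test is about 5.6%, 8% or 11%. If 0.05 to 0.10 is instead taken as a share of single-visit variance, simulation gives about 9% to 14%. The 5% in the table is therefore a floor that holds only without a facility effect.

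**The case against.** The strongest reply is that the article condenses a fuller plan, and turning repeated ratings into an analysis variable is often left to the SAP. The text also leans towards the harmless reading: the sample size counts participants per condition, and a t-test on carer means is valid at the carer level, as the table shows. The two-way ANOVA has an unnamed second factor that could be visit or time, and the facility is given only as an example of a higher level.

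Much of this stands. A reader might infer that the plan intends to pool some 240 ratings, or to claim success on any visit, and so carries a false-positive rate near 30%. The documents do not support that. Neither analysis is stated, and 30% is the pooled rate at an assumed correlation of 0.5. Nor can one say that no analysis in the section could ever fit, because the second ANOVA factor is open. The assumed effect of 0.5 SD is also not the protocol's; its only planning effect is 0.80, on a secondary measure.

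What does not stand is that this is mere silence. The article names its lead test, applies it to the outcome measures in general, and fixes a primary measure with a structure that this test does not handle without a further step. Even if the second factor is visit, the t-tests listed first remain undefined for this measure, and carer is still not named as a level.

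**Conclusion.** The point holds in a limited form. As specified, no analysis fits visit ratings nested in carers nested in randomised facilities. The natural reading, one mean per carer, keeps about 5% error if facilities do not differ, and somewhat more if they do. Other readings that the text permits but does not plan range from about 14% to 39% error, or lose power through use of a single visit. All these figures depend on an assumed within-carer correlation, and the power figures also on an assumed effect. They show how much room the wording leaves; they do not give the trial's actual error rate. The point is worth correcting because it concerns the primary measure and the correction is cheap.

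**What to change.** In the Statistical analysis section, replace the independent t-test for the primary measure with one named contrast: the difference between conditions in mean visit score over W2-W4.

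- **Instrument.** Name either visit satisfaction or visit mastery as primary and make the other secondary. The article gives no rule for combining them, and two independent tests at 0.05 would give 1 - 0.95^2 = 9.75%.
- **Model.** Estimate the contrast from a linear mixed model of the visit ratings, with random intercepts for carer and facility. This also accommodates unequal numbers of visits per carer. Use small-sample degrees of freedom, since 50 carers in training groups of up to six imply few facilities.
- **Other analyses.** Report visit-by-visit results as descriptive, and name the second factor of the two-way ANOVA if that analysis is kept.

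The cost is a few sentences and slightly more modelling, with no new data. The interval will probably be wider once facility is included.
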